### Sample size

To calculate the sample size, we considered the two primary outcomes: DPT3 coverage among 6–23 month old children and FIC among 12–23 month age group. Per our initial (pre-baseline) sample size calculation, we needed 120 villages per group, intervention and control, leading to a total of 240 villages, to detect a difference of at least 10 percentage points in coverage between the two groups, with 80% statistical power using a two-sided test at 5% level of significance, after accounting for the correlation in immunization status among children from the same village. We considered an equal allocation of 240 villages across 3 districts, resulting in 40 intervention and 40 control villages in each of the selected districts. Estimates of the coverage rate for DPT3 and FIC in the control group were obtained from the most recent data available at the time (RSOC, 2013–14) [2]. In Assam, the estimates were 65.9% and 55.3% for DPT3 and FIC, respectively. If the coverage rates for DPT3 and FIC in the intervention group are at least 10 percentage points higher, i.e., 75.9% and 65.3%, respectively, our sample size would allow us to detect the difference in coverage rates between the two groups. To calculate the intracluster correlation (ICC) for these outcomes, we extracted DLHS-3 (2007–08) [28] unit level data for Assam and obtained the estimates as 0.21 and 0.25 for DPT3 and FIC, respectively. We further assumed that a village will have a minimum of 15 children 6–23 month old and 10 children 12–23 month old. If there were more than 15 eligible children in a village, we randomly selected 15 children. Baseline survey was conducted in all 240 villages, as per the requirement of pre-baseline sample size calculation.

### Up-to-date ICC and re-estimation of sample size

Sample size is sensitive to the estimate of ICC used in the calculation. ICC, often interpreted as the degree of homogeneity of units within cluster with respect to the outcome variable, is defined as the ratio of between-cluster variability to total variability in the outcome. ICC estimates used in the pre-baseline sample size calculation were based on DLHS-3 (2007–08) data. We expected the recent ICC estimates for DPT3 and FIC to be different, most likely smaller in magnitude because of the improved reach of maternal and child health services, including immunization, under the National Rural Health Mission (NRHM, 2005–2012) [29]. Immunization service delivery, supply chain system, vaccine logistics and the process of linking health system and communities through ASHA- all these have been standardized to a large extent in all rural areas. Moreover, the recent estimates for coverage rate for DPT3 and FIC may have also changed. These changes would affect the sample size needed to detect a difference in coverage rates between the control and intervention groups.

On another note, our intervention is complex in nature, involves sustained interaction over several months with the community. Owing to this intense nature of our intervention, there were concerns that implementation of the intervention may not happen optimally within the timeframe and budget if the sample size was unnecessarily large. The international panel of reviewers of this study also recommended that the sample size and ICC be recalibrated based on new data that would become available to us from the baseline survey. These considerations led us to recalculate the sample size based on recent estimates derived from baseline data.

Table 2 presents the revised estimates based on data from baseline survey and the revised sample size. Note that the ICC estimates based on baseline data have decreased relative to earlier estimates from DLHS-3, as anticipated. On the other hand, vaccination coverage rates have increased substantially relative to RSOC data (2013–14). This sudden increase in vaccination coverage can perhaps be attributed to Mission Indradhanush (MI), a flagship program of the Ministry of Health and Family Welfare (MoHFW) and was also observed in other historically poor-performing states such as Bihar, Rajasthan and Madhya Pradesh [30]. Two phases of MI happened before our baseline survey (phase 1: April–July 2015 and phase 2: Nov 2015-Feb 2016) and all three study districts (Bongaigaon, Kamrup rural, and Udalguri) received at least one round of MI intervention. However, it is possible that this high level of immunization coverage will not be sustained in future after the supplementary immunization activities under MI are discontinued. In view of these high coverage rates, we reduced the minimum detectable difference from 10 to 8 percentage points in the revised calculation of sample size.

**Table 2 Tab2:** Revised sample size for two primary outcome variables based on SALT baseline survey (July–August 2016) data

Outcome of interest	Updated coverage rate (%)	Updated ICC	Updated sample size (number of villages in each of intervention and control group)
DPT3	84	0.17	57
FIC	79	0.18	90

Per our revised sample size calculation, we needed 90 villages per group to detect a difference of at least 8 percentage points in coverage between the control and intervention groups with 80% statistical power based on a two-sided test having 5% level of significance, after accounting for the correlation in immunization status among children from the same village. Total number of villages required for the study is 180 (90 × 2). We considered an equal allocation of 180 villages across the 3 districts, resulting in 30 intervention and 30 control villages in each of the three selected districts.

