Child has vaccination card	92.7	92.4	0.7852	92.1	92.1	0.9731
Child (12–23 month old) is fully immunized	78.5	77.6	0.8244	77.6	77.6	0.8479

*Wilcoxon Rank Sum Test with Null Hypothesis: location parameters of the distribution are the same in each group

^a^*HS* higher secondary

To check balances between intervention and control groups based on selected household, mother and child level characteristics we have adjusted for clustering as responses from HHs (as well as mothers and children) within a village are correlated. However, for checking balance based on village level indicators this adjustment does not have any impact on standard errors and hypothesis testing. All analysis has been done using “survey” package [35] in R [36]. Wilcoxon rank sum test has been adjusted as per the survey design [37].

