Our community engagement intervention; the SALT approach is participatory, interactive, prolonged and involves multiple inter-related steps. RCTs of complex interventions like SALT are often criticised as being ‘black box’ as it can be difficult to know why and how the intervention worked (or not) [40]. At the end of the study, the absence of an impact could be simply because SALT was ineffective in this particular context or it could potentially be because of less than optimal implementation of the intervention. In order to be able to answer this, we will attempt to ‘unpack’ the ‘black box’ by examining underlying processes. To that end, we developed a process evaluation data collection plan for the entire duration of the intervention phase. Specifically, the aim is to answer the following questions: 1) whether the intervention is implemented as intended, 2) whether the intervention incorporates the primary objective of the study (i.e., increasing immunization coverage), 3) consistency of intervention delivery across communities in terms of the process of administering the intervention, 4) how the intervention was received by the HHs and communities across villages and districts, and 5) whether contextual factors influence the implementation of intervention.

As per our revised sample size (90 villages per group), our study is powered to identify a difference of at least eight percentage points in immunization coverage between the intervention and control groups. Any effect size below that may not be detected and, hence, the intervention may be declared as ineffective. It is true that larger the sample size, higher is the chance of detecting a difference, even one that is smaller than the expected difference. We had to tally these methodological considerations against few practical considerations, which also could affect the quality of evidence.

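### The revised sample size assumes a baseline full immunization coverage of 79%, which Table 3 does not reproduce (about 78% overall, 77.6% after discarding); at the Table 3 rates, 90 villages per group give about 78% power rather than 80%

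*Protocol article*

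**What the plan says.** The section on up-to-date ICC and re-estimation of sample size introduces its inputs thus: "Table 2 presents the revised estimates based on data from baseline survey and the revised sample size". The Table 2 row for FIC gives 79% coverage, ICC 0.18 and 90 villages per group. The other primary outcome needs fewer villages ("DPT3 84 0.17 57"), so FIC sets the size of the trial. The target was also changed: "we reduced the minimum detectable difference from 10 to 8 percentage points in the revised calculation of sample size". The conclusion is that "we needed 90 villages per group to detect a difference of at least 8 percentage points in coverage between the control and intervention groups". The error rates attached to that conclusion read "with 80% statistical power based on a two-sided test having 5% level of significance".

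Table 3, in the section on balancing checks, is also built from baseline data. Its row "Child (12–23 month old) is fully immunized" reads 78.5% control and 77.6% intervention over the 240 baseline villages, and 77.6% in each arm after discarding.

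On future coverage, the re-estimation section says that "it is possible that this high level of immunization coverage will not be sustained in future". The Discussion then says, with no condition on coverage, that "our study is powered to identify a difference of at least eight percentage points in immunization coverage".

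**The concern.** Two tables drawn from one survey, for one age group, give different values for the input that fixes the number of villages. A mean of 78.5 and 77.6 cannot exceed 78.5, and with arms of about equal size it is about 78. So 79% is not the pooled baseline rate that Table 3 implies, and the article does not say what else it might be.

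The direction matters. Above 50%, a lower coverage rate means a larger binomial variance, so for a fixed 8-point difference a lower control rate needs more villages. The Discussion says that effects below 8 points may be missed and the intervention declared ineffective, so the power figure is what a null result will be read against.

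**Working it through.** **Inputs.** Two-sided 5%, 80% power, 8-point difference, FIC 79% and ICC 0.18 come from the re-estimation section and Table 2. The cluster size of m = 10 children aged 12–23 months comes from the Sample size section. The alternative FIC rates come from Table 3.

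**Formula.** With V = p₁(1−p₁) + p₂(1−p₂) and p₂ = p₁ + 0.08:
- children per arm before clustering: n = (1.96 + 0.8416)² × V / 0.08² = 7.849 × V / 0.0064
- design effect: 1 + 9 × 0.18 = 2.62
- villages per arm: n × 2.62 / 10
- power with 90 villages: Φ(0.08/SE − 1.96), with SE = √(2.62 × V / 900)

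**Reproducing the plan's figure.** At 79% against 87%, V = 0.1659 + 0.1131 = 0.2790, n = 342.2 and villages = 89.6, so 90. A pooled-variance version gives 90.4. The same formula gives 57.5 for DPT3 (m = 15, ICC 0.17; stated 57) and 120.9 for the pre-baseline FIC calculation (55.3%, 10 points, ICC 0.25; stated 120). All agree to within one village, so this is in substance the formula used.

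**Replacing only the FIC rate.** The whole-sample value is (78.5 + 77.6)/2 = 78.05%.

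| Control FIC | V | Villages per arm | Power with 90 per arm | Difference detectable at 80% |
|---|---|---|---|---|
| 79% (Table 2) | 0.2790 | 89.6 | 80.2% | 8.0 points |
| 78.5% (control arm, 240 villages) | 0.2856 | 91.8 | 79.2% | 8.1 points |
| 78.05% (both arms, 240 villages) | 0.2914 | 93.6 | 78.4% | 8.1 points |
| 77.6% (after discarding) | 0.2971 | 95.5 | 77.6% | 8.2 points |

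With the pooled variance, power at 79%, 78.05% and 77.6% is 79.8%, 78.1% and 77.3%.

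**Number of retained villages.** The first three village-level rows of Table 3 are yes/no properties of a village. If unweighted, each percentage should be a whole number of villages over the arm's total.
- Control after discarding: 39.8, 29.6 and 31.6 equal 39/98, 29/98 and 31/98.
- Intervention after discarding: 41.7, 26 and 35.4 equal 40/96, 25/96 and 34/96.
- A total of 90 does not fit: 35/90 = 38.9 and 36/90 = 40.0, so 39.8 cannot occur.

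With 98 and 96 villages, power at 77.6% would be 80.7%. This inference needs care. The same test on the 240-village columns fits 120 for intervention (47, 30 and 45 of 120), but the control value 40.5 cannot come from 120 villages (48/120 = 40.0, 49/120 = 40.8). Something other than a plain village count may therefore lie behind these rows.

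**The case against.** The strongest reply is that 90 is correct arithmetic from its stated inputs, and that the disputed input moves power very little. Both parts stand. The 77.6% rate also could not have been the input to Table 2, because the retained set was chosen only after the required number was known. The fair comparison for the calculation as made is the full baseline sample, where the shortfall is under 2 points. Rounding and conservative inputs are of the same size: at 78.05%, an ICC of 0.17 gives 79.8% power, and 11 children per village instead of the stated minimum of 10 gives 79.6%. Table 3 was analysed with survey-design methods, so the two tables may use different estimators. If 98 and 96 villages were really kept, the shortfall disappears. None of this explains the 79%. It does mean that the article does not show which table is wrong, so 77.6% should not simply be substituted.

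A reader might also infer that the document expects coverage to fall and that power then collapses. The text does not support that: it calls a fall possible and gives no size. Holding 8 points, ICC 0.18 and 90 villages, power would be 67% at an assumed control FIC of 70% and 57% at 55.3%, the earlier Assam figure. Those rates are assumptions, and so is the fixed difference. The document itself lowered its target because coverage was high. If the intervention reached the same share of unimmunized children (8 of 21), the difference at 70% would be 30 × 8/21 = 11.4 points and power 94%.

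**Conclusion.** The discrepancy is real, falls on the input that determines the sample size, and is unexplained. Its effect is modest: with 90 villages per arm and 8 points, power is about 78.4% at the whole-sample rate and 77.6% at the post-discard rate, against a stated 80%, a loss of about 1.6 to 2.4 points. The detectable difference rises to between 8.1 and 8.2 points. This rests on ICC 0.18, 10 children per village, an 8-point difference and 90 villages per arm, and the last of these is itself in some doubt from Table 3.

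The Discussion's statement is firmer than its basis. It holds only if control FIC at endline is near the baseline rate, and the article itself says that may not be so. This is a reporting correction. It does not show that the trial is materially underpowered, and the absence of a power table over lower coverage rates is not an error in a protocol article.

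**What to change.** 1. Reconcile the 79% in Table 2 with the FIC row of Table 3, stating for each the sample, estimator and weighting used.
2. State how many villages were retained in each arm, and reconcile that count with the 180 in the Table 3 column heading.
3. Restate the power or the detectable difference at the reconciled rate and count. If 90 per arm and about 78% stand, that is about 78% power for 8 points.
4. In the Discussion, make the power statement conditional on control FIC staying near its baseline level. If power at lower coverage is quoted, label the coverage and the fixed 8-point difference as assumptions.

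No villages need be added and the design does not change. The cost is a few lines of text and, unless the retained count proves higher than 90 per arm, a slightly less favourable power figure.

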### Qualitative component

To evaluate the impact of the intervention, our study includes a qualitative component to complement the quantitative surveys. As a part of qualitative data collection, focus group discussions (FGDs) and key informant interviews (KIIs) were conducted at baseline. The purpose of the FGDs and KIIs was to understand community perceptions regarding immunization, perceptions on immunization of different stakeholders and to gain an understanding of current community engagement if at all.

A more extensive qualitative data collection is planned for endline. FGDs and KIIs will be conducted in a sub-sample of villages in the intervention and control arms that will be representative of villages across the 4 strata identified in three districts. The goal is to examine if, how and why the community mobilized to take ownership of child health and immunization related issues, the perceived benefits and challenges of SALT approach, the perceived improvements in child health with a focus on immunization, and whether the community identifies SALT as a valuable, feasible and sustainable approaches to address community problems.

### Randomization strategy

We adopted a restricted randomization strategy, specifically stratified randomization, to achieve better balance, leveraging information available to us prior to allocation. As opposed to a complete randomized allocation, stratification has the potential to provide explicit balancing of potentially important covariates known to be associated with coverage outcomes, as randomization happens within each stratum [31].

All 240 villages sampled in the baseline survey were randomized to the intervention and control groups. For our stratified randomization strategy, the key advantage of randomization post-baseline survey is that the stratification of villages, and subsequently randomization within stratum, can be based on up-to-date indicators obtained from the baseline data.

Sampled villages from baseline survey, within a district, were stratified into four strata based on a composite score constructed using the following village-level indicators: average number of under-5 children, percentage of HHs living for more than 50 years in the village, percentage of SC HHs, percentage of ST HHs, percentage of Muslim HHs, percentage of HHs belonging to the poorest wealth quintile, percentage of HHs belonging to the richest wealth quintile, percentage of mothers having no formal schooling, percentage of mothers with educational qualification higher secondary or more, percentage of mothers receiving full antenatal care during pregnancy, village had flood last year or not. Full antenatal care is defined as consumption of IFA tablet/syrup for 100+ days, 3+ antenatal check-ups visits, and receipt of at least one TT injection. These indicators were derived based on data from baseline survey.

All indicators were not used for stratification within a district, the choice of variables depended on the district-specific context. For example, in Kamrup rural, all three socio-demographic indicators— percentage of SC HHs, percentage of ST HHs, and percentage of Muslim HHs, were considered whereas for Bongaigaon percentage of ST HHs was not relevant and for Udalguri only percentage of ST HHs was relevant.

To define economic indicators, wealth index was constructed for each household using baseline data. Wealth index is a widely accepted measure of household’s long term economic status [32, 33]. To construct the wealth index, we considered variables related to housing characteristics, sanitation facility of the HH, and asset possession. Each variable is assigned a weight generated through principal component analysis (PCA) and the standardized variables are multiplied by the weights and summed to produce the wealth index. The first principal component, explaining 25% of the total variation in the data, was considered as the wealth index. Based on the wealth index the HHs were divided into quintiles: poorest, poorer, middle, richer, and richest.

Finally, within each stratum we randomized sampled villages to intervention and control groups. After stratification within a district, each stratum contained 20 villages as the baseline sample covered 80 villages in each district. We randomly selected 10 villages to receive the intervention and the remaining 10 villages will continue to receive immunization services from the routine immunization program in place (control group). The flowchart in Fig. 2 illustrates the randomization procedure (in orange). R statistical software was used to implement the randomization strategy through the use of random numbers [34].

### Minimizing intervention-control contamination

In each district, we had randomized the 80 sampled villages to the intervention and control groups in equal proportion. However, according to our revised sample size calculation, we needed only 30 intervention and 30 control villages, that is, we had the liberty to exclude 10 villages from each of the two groups. We attempted to use this opportunity to minimize intervention-control contamination while excluding villages, as opposed to random exclusion.

Transfer of knowledge is a crucial component of SALT intervention. Particularly, during the knowledge fair, the community may have an opportunity to meet peers from the control community and share their knowledge and experience, in case intervention and control villages are located in close proximity. To mitigate potential contamination between intervention and control villages, we attempted to ensure that the intervention and control villages are sufficiently far apart from one another. For our community-based intervention, by separating the intervention and control villages geographically we seek to reduce the chances of interaction between community members belonging to the intervention and control groups. The following procedure was used to ensure geographical buffer between intervention and control villages.

After randomization, we plotted the intervention and control villages on Google Maps by uploading an excel file of villages having locations (defined by “village name, district name, state name”) as a column. Different-color place marks were used for intervention and control villages. Using features of Google Maps, we then calculated straight line distances between intervention and control villages when they visibly appeared to be close by. If the distance is less than 3 km (KM), we discarded one of the villages. While discarding villages, we were mindful about two things: 1) an equal number of intervention and control villages are being discarded and 2) distribution of intervention and control villages across strata does not change significantly as that might have an impact on balance between the two groups.

Figure 4 illustrates the procedure using two Google Maps screenshots. In Panel a, we plot all 80 villages from Udalguri district that were randomized to intervention (green) and control (red) groups and in Panel b we present the same plot after discarding villages in instances where intervention and control villages are within 3 KM distance. For example, in bottom left corner, two control villages appeared to be located in close proximity to three intervention villages. Distance calculation confirmed that the straight line distance is less than 3 KM and, hence, two control villages were discarded (circled in blue in Panel a and b). Using the same rationale, two intervention villages were also discarded as seen in the top left and top middle part of the plot (circled in blue in Panel a and b).

